### Randomization and blinding

#### Randomization

Random allocation was performed using the centralized randomization system of Zhejiang Provincial Hospital of Traditional Chinese Medicine. Eligible participants who met all inclusion criteria were assigned to either the electroacupuncture group or the sham needle plus sham electroacupuncture group in a 1:1 ratio, with 39 participants allocated to each group.

#### Blinding

This study adopts a single-blind design in which participants, outcome assessors, and statistical analysts are blinded to group allocation. Participants are treated in separate rooms to minimize communication. Acupuncturists receive standardized training and follow semi-structured communication procedures to avoid disclosure of group assignment. Outcome assessments are conducted strictly according to predefined case report form procedures. An independent statistician blinded to allocation performs all analyses.

Emergency unblinding will be permitted only when necessary for participant safety. All unblinding procedures require approval from the principal investigator and are fully documented. Participants who undergo emergency unblinding will be excluded from efficacy analyses but retained in safety analyses.

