**Methods:**

This single-blind, randomized, controlled trial will enroll 78 adults with chronic insomnia disorder (ICSD-3TR) who have used NBZDs for >6 months. Participants will be assigned 1:1 to electroacupuncture or sham electroacupuncture. Both groups will undergo a standardized, gradual NBZDs tapering protocol over 6 weeks and receive standardized sleep hygiene education. Participants in the electroacupuncture group will receive electroacupuncture treatment three times per week at predefined acupoints (Baihui, Sishencong, Anmian, Shenting, Yintang, Hegu, Taichong, Neiguan, Shenmen, Sanyinjiao, Shenmai, and Zhaohai), whereas participants in the control group will receive non-penetrative sham electroacupuncture. The primary outcome is the successful discontinuation rate of NBZDs at the end of the 6-week treatment period. Secondary outcome measures included subjective sleep scales, objective sleep parameters (polysomnography and actigraphy), and daytime functioning assessments, among others. Safety will be assessed through systematic monitoring and documentation of adverse events. Statistical analyses will follow the intention-to-treat principle using mixed-effects models.

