### Withdrawal criteria

Participants will be withdrawn from the study if any of the following occur:

(1) Participants who develop intolerable severe withdrawal symptoms during the NBZDs tapering process.(2) Voluntary withdrawal at the participant’s request.(3) Withdrawal of informed consent.(4) Emergence of exclusion criteria during the study period.(5) Poor treatment compliance, defined as attendance at fewer than 50% of scheduled acupuncture sessions.(6) Occurrence of adverse events that preclude continued participation or pose a risk to participant safety.

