### Outcome measures

#### Primary outcome measures

The successful discontinuation rate at the end of the 6-week treatment was defined as the proportion of patients who had completely ceased NBZDs use (any dose) during the final week of treatment (days 36–42). Medication adherence was verified using patients’ daily diaries and medication records. Patients completed a daily diary card, on which they recorded the date, medication name, dose, time of administration, and any adverse reactions. The diary cards were returned to the physician at each weekly visit, and prescription records were cross-checked by an independent observer every 3 weeks. Any discrepancy between the diary and medication records will be resolved by consensus of two blinded independent investigators based on all available data (daily diaries, medication records). Urine or blood drug concentration testing was not performed to confirm participants’ self-report of hypnotic discontinuation, due to the short half-life of NBZDs (requiring daily sampling, which is logistically infeasible) and the increased participant burden that would likely raise dropout rates. The multi-source adjudication approach described above was considered a reliable alternative.

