### Data management

Data collection will encompass three aspects: (1) Participants independently completing relevant scale assessments in the acupuncture treatment room. The assessment requires approximately half an hour. During this period, participants may consult dedicated assessment physicians regarding any questions. (2) Participants will complete sleep diaries at home throughout the study period under physician guidance.

This study will train data outcome assessors to enhance participant compliance, collect high-quality complete datasets, and facilitate follow-up completion. Dedicated personnel will perform data entry, receiving specialized training in data input procedures, coding protocols, and secure storage practices. Data analysts in this study will receive training in data evaluation and analysis methodologies. This study strictly safeguards participant privacy through the following primary measures: ① Requiring participants to provide only research-related personal information during the study process; ② Store data on designated computers with restricted access, ensuring the specific folders containing data are password-protected; ③ Only personnel involved in the research can access participants’ personal information, and this information will be destroyed upon completion of the study.

The full analysis set (FAS) will include all randomized participants who receive at least one treatment session and have at least one post-baseline assessment, consistent with the intention-to-treat principle. Missing outcome data will be handled using likelihood-based estimation within mixed-effects models under the missing-at-random assumption. Multiple imputation will be conducted as a sensitivity analysis. The safety set (SS) will include all participants who receive at least one treatment session. The pilot data and the main trial data will be pooled after completion of the main trial to conduct sensitivity analyses assessing the robustness of the conclusions.

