### Statistical analysis

All statistical analyses will be conducted using SPSS version 28.0 (IBM Corp., Armonk, NY, United States) according to the intention-to-treat principle. A two-sided *p* < 0.05 will be considered statistically significant.

Continuous variables will be summarized as mean ± standard deviation or median (interquartile range), as appropriate. Categorical variables will be presented as frequencies and percentages. Between-group differences at single time points will be assessed using independent-samples *t*-tests or Mann–Whitney U tests for continuous variables and *χ*^2^ or Fisher’s exact tests for categorical variables.

Longitudinal outcomes will be analyzed using linear mixed-effects models with fixed effects for group, time, and group-by-time interaction, and random intercepts for participants. Missing data will be handled using likelihood-based estimation under the missing-at-random assumption. Multiple imputation will be conducted as a sensitivity analysis.

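### Dropping emergency-unblinded participants from efficacy contradicts the protocol's intention-to-treat statements and its own full analysis set

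*Protocol article*

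**What the plan says.** Four statements in the protocol article bear on who enters the efficacy analysis.

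- Abstract, Methods: "Statistical analyses will follow the intention-to-treat principle using mixed-effects models".
- Statistical analysis: all analyses are to be done "according to the intention-to-treat principle".
- Data management: the FAS "will include all randomized participants who receive at least one treatment session and have at least one post-baseline assessment, consistent with the intention-to-treat principle". Unblinding is not mentioned.
- Blinding: "Emergency unblinding will be permitted only when necessary for participant safety", and then "Participants who undergo emergency unblinding will be excluded from efficacy analyses but retained in safety analyses".

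The primary outcome is binary: no NBZD use at any dose in days 36–42. It is established from daily diaries and prescription records, with discrepancies adjudicated by two blinded investigators. Missing data are to be handled by likelihood estimation in mixed models under missing-at-random, with multiple imputation as a sensitivity analysis.

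**The concern.** Intention-to-treat keeps each randomised participant in the comparison whatever happens afterwards. The Blinding rule removes people because of something that happens afterwards, and that something is a safety problem. In a drug taper, a safety problem is unlikely to be unrelated to whether the person stops the drug. The Safety evaluation section counts withdrawal reactions among the adverse events, and the first Withdrawal criterion is "Participants who develop intolerable severe withdrawal symptoms during the NBZDs tapering process".

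If the removed people are mainly failures and come more from one arm, that arm's success rate rises for a reason unrelated to treatment. The mixed-model and missing-at-random provisions do not repair this, because they act only on people who remain in the analysis set.

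The FAS raises a milder form of the same point. It leaves out randomised participants with no session or no post-baseline assessment, yet it is described as consistent with intention-to-treat. It is a modified intention-to-treat set.

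**Working it through.** **Step 1: the rules side by side.** Take a participant who is randomised, attends at least one session, has at least one post-baseline assessment and is then unblinded for safety.

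| Source | In the efficacy analysis? |
|---|---|
| Abstract; Statistical analysis (intention-to-treat) | Yes |
| Data management (FAS) | Yes |
| Blinding | No |

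All three cannot be followed. This conflict needs no arithmetic.

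**Step 2: inputs for the size.** The protocol gives no expected number of unblindings, so there is no stated figure to reproduce. From the Sample size section: 39 per arm, two-sided α = 0.05, expected success 50.00% vs 10.83%, which is 0.50 × 39 = 19.5 and 0.1083 × 39 = 4.2 successes. Assumed for illustration: the numbers removed, and that everyone removed is a failure.

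**Step 3: effect on one result.** For success/failure counts a, b (electroacupuncture) and c, d (sham), with total N, uncorrected chi-square = N(ad − bc)² / [(a+b)(c+d)(a+c)(b+d)]. Assume 14 and 7 successes.

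| Failures removed | Table | Rates | Chi-square | p | Fisher p |
|---|---|---|---|---|---|
| None | 14/39 vs 7/39 | 35.9% vs 17.9% | 78 × 273² / (39 × 39 × 21 × 57) = 3.19 | 0.074 | 0.125 |
| 4 electroacupuncture | 14/35 vs 7/39 | 40.0% vs 17.9% | 74 × 301² / (35 × 39 × 21 × 53) = 4.41 | 0.036 | 0.043 |
| 4 per arm | 14/35 vs 7/35 | 40.0% vs 20.0% | 70 × 245² / (35 × 35 × 21 × 49) = 3.33 | 0.068 | 0.117 |
| 4 sham | 14/39 vs 7/35 | 35.9% vs 20.0% | 74 × 217² / (39 × 35 × 21 × 53) = 2.29 | 0.130 | 0.196 |

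Balanced removal leaves the test almost where it was. One-sided removal moves it towards the arm that loses more failures.

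Near the planned rates nothing changes. 20/39 vs 4/39 gives Fisher p = 0.0002. Removing four failures gives p below 0.0001 if all come from electroacupuncture and 0.0004 if all come from sham.

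**Step 4: false-positive rate.** This is by exact enumeration of the uncorrected chi-square test, 39 randomised per arm, equal true success rates, nominal 5%, all removed participants failures.

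| True rate, both arms | None removed | 4 per arm | 4 from one arm | 6 from one arm | 8 from one arm |
|---|---|---|---|---|---|
| 10.83% | 5.8% | 5.8% | 4.7% | 5.6% | 7.2% |
| 30% | 5.3% | 5.8% | 6.6% | 9.5% | 11.3% |
| 50% | 5.4% | 6.0% | 8.6% | 13.3% | 20.7% |

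At a low common success rate there is little inflation. At 30% or above, four or more one-sided removals begin to matter.

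**The case against.** The strongest reply is that the rule will seldom operate. The protocol deals with intolerable withdrawal symptoms through provisions in the tapering section and the Withdrawal criteria, and neither requires knowledge of the allocation. Both arms follow the same taper, the sham delivers neither penetration nor current, and each unblinding needs the principal investigator's approval. The pilot reported no serious adverse events in 10 patients. So the count is probably small. That stands, and it limits the expected size of the bias. It does not remove the contradiction.

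A reader might infer that the rule selectively removes failures. The documents do not establish this. They do not say who will be unblinded, do not tie unblinding to failure and show no imbalance between arms. It is a plausible inference from the safety trigger, and no more. Imbalance is possible, since only one arm receives penetrating needles and current, but it is not shown.

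A reader might also infer that a handful of exclusions would readily overturn the result. That depends on the table and the test. For 11/39 vs 4/39, removing three electroacupuncture failures takes Fisher p from 0.083 to 0.042, but the uncorrected chi-square is already 0.044 before any removal. The protocol allows either test for categorical comparisons.

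On the FAS, requiring one session and one post-baseline assessment is common and openly stated. The medication diary is scheduled every week, so few treated participants should lack any record. What remains there is mainly the label. Nor can everyone left out simply be classified from records: a person with no diary for days 36–42 needs an imputation rule.

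**Conclusion.** The point holds as an internal contradiction. The Blinding section imposes a post-randomisation, safety-triggered exclusion from efficacy that conflicts with the intention-to-treat statements and with the FAS definition. It can bias the primary comparison if unblindings are unequal between arms.

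The size is conditional. In the assumed 14 vs 7 table, four one-sided removals cross 0.05 under both tests, while four per arm do not. At the planned success rates the conclusion would not change. These results assume that every removed participant is a failure, and the numbers removed are assumptions too. The FAS wording is a secondary labelling matter.

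**What to change.** 1. Delete the sentence in Blinding that excludes emergency-unblinded participants from efficacy.
2. Define the primary efficacy set as all 78 randomised participants, analysed as allocated. Determine status in days 36–42 from the diary and prescription records, and count unknown status as not discontinued. Add multiple imputation of unknown status as a sensitivity analysis.
3. Keep the present FAS, labelled modified intention-to-treat, and the analysis without unblinded participants as sensitivity analyses only. Report the number of unblindings by arm.

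The cost is one deleted sentence and one changed definition, with no extra participants. The reported success rate may be slightly lower. With 39 per arm and 50% vs 10.83%, power is 97.7% (pooled-variance normal approximation). As a hard case, suppose the whole 20% dropout allowance in each arm counts as failure, so the rates become 0.8 × 50% = 40% and 0.8 × 10.83% = 8.66%. With mean rate 0.2433, power = Φ[(0.3134 − 1.96 × √(2 × 0.2433 × 0.7567 / 39)) / √((0.40 × 0.60 + 0.0866 × 0.9134) / 39)] = Φ(1.36), about 91%, still above the planned 90%.

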### Data management

Data collection will encompass three aspects: (1) Participants independently completing relevant scale assessments in the acupuncture treatment room. The assessment requires approximately half an hour. During this period, participants may consult dedicated assessment physicians regarding any questions. (2) Participants will complete sleep diaries at home throughout the study period under physician guidance.

This study will train data outcome assessors to enhance participant compliance, collect high-quality complete datasets, and facilitate follow-up completion. Dedicated personnel will perform data entry, receiving specialized training in data input procedures, coding protocols, and secure storage practices. Data analysts in this study will receive training in data evaluation and analysis methodologies. This study strictly safeguards participant privacy through the following primary measures: ① Requiring participants to provide only research-related personal information during the study process; ② Store data on designated computers with restricted access, ensuring the specific folders containing data are password-protected; ③ Only personnel involved in the research can access participants’ personal information, and this information will be destroyed upon completion of the study.

The full analysis set (FAS) will include all randomized participants who receive at least one treatment session and have at least one post-baseline assessment, consistent with the intention-to-treat principle. Missing outcome data will be handled using likelihood-based estimation within mixed-effects models under the missing-at-random assumption. Multiple imputation will be conducted as a sensitivity analysis. The safety set (SS) will include all participants who receive at least one treatment session. The pilot data and the main trial data will be pooled after completion of the main trial to conduct sensitivity analyses assessing the robustness of the conclusions.

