### NBZDs tapering protocol

Based on the 2025 European clinical practice guideline recommending a gradual dose reduction of 10–25% per week for NBZDs (27), and supported by two clinical studies that successfully employed a weekly 25% reduction strategy (21, 28), NBZDs will be reduced at a rate of 25% of the baseline dose per week. If participants experience intolerable withdrawal symptoms during tapering—such as exacerbation of insomnia, anxiety, or agitation—the dose will be temporarily reverted to the previous level. Tapering will be reattempted during the subsequent evaluation cycle (1 week per cycle).

Throughout the treatment period, participants will attend weekly in-person consultations and receive twice-weekly telephone follow-ups. Dose adjustments will be conducted through a shared decision-making process, enabling participants to actively engage in symptom monitoring and self-management under physician supervision. Final dosage modifications will require investigator approval.

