### Efficacy evaluation criteria

① Primary Efficacy Outcome Measures

The primary efficacy outcome is the successful discontinuation rate of NBZDs at the end of the 6-week treatment period. Between-group differences in discontinuation rate will be evaluated using regression-based methods appropriate for binary outcomes.

② Secondary Efficacy Outcome Measures

a. Subjective Sleep Efficacy Evaluation

Subjective sleep outcomes, including the Insomnia Severity Index (ISI) and Pittsburgh Sleep Quality Index (PSQI), will be analyzed using longitudinal mixed-effects models incorporating repeated measurements across predefined study time points to estimate treatment effects over time.

b. Objective Sleep Efficacy Assessment

Objective sleep parameters derived from PSG and ACT will be analyzed using longitudinal mixed-effects models to account for within-subject correlation and to evaluate changes across study time points.

c. Daytime Functioning Assessment

Daytime functioning outcomes will be analyzed using longitudinal mixed-effects models to assess treatment effects across time.

d. NBZDs Reduction Response Evaluation

Medication reduction responses, including NBZDs reduction rate, withdrawal symptoms, and craving scores, will be evaluated using regression-based models appropriate to outcome type, with longitudinal modeling applied where repeated measurements are available.

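### The only missing-data rule assumes missing at random and makes no exception for the single week-6 discontinuation outcome, although one withdrawal criterion removes participants because the taper failed

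*Protocol article*

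**What the plan says.** All references are to the Protocol article.

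- **Primary outcome** (Primary outcome measures): the proportion who have "completely ceased NBZDs use (any dose) during the final week of treatment (days 36–42"). Table 1 marks it at week 6 only.
- **Primary analysis** (Efficacy evaluation criteria): "Between-group differences in discontinuation rate will be evaluated using regression-based methods appropriate for binary outcomes".
- **Missing data** (Data management, repeated under Statistical analysis): "Missing outcome data will be handled using likelihood-based estimation within mixed-effects models under the missing-at-random assumption", followed by "Multiple imputation will be conducted as a sensitivity analysis". The abstract adds: "Statistical analyses will follow the intention-to-treat principle using mixed-effects models". The primary outcome is not exempted.
- **Withdrawal criteria**: criterion 1 is "Participants who develop intolerable severe withdrawal symptoms during the NBZDs tapering process"; criterion 5 is "Poor treatment compliance, defined as attendance at fewer than 50% of scheduled acupuncture sessions". The others are voluntary withdrawal, withdrawn consent, an emerging exclusion criterion and adverse events.
- **NBZDs tapering protocol**: when withdrawal symptoms become intolerable, "the dose will be temporarily reverted to the previous level" and the reduction is tried again in the next weekly cycle.
- **Sample size**: 50.00% against 10.83%, 32 per group, raised to 39 for 20% dropout.

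The article does not say how a withdrawn participant is counted for the primary outcome, or whether NBZD use is recorded after withdrawal.

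**The concern.** The missing-data rule is built for repeated measurements, where a participant's earlier values inform the missing one. The primary outcome has no earlier values of its own. Applied to it, the rule leaves a participant without a week-6 value out of the estimate.

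For criterion 1 the reason for leaving is failure of the taper, which is what the outcome measures. Treating that person as missing at random gives them the success probability of those who stayed.

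At stake is the one outcome the trial is sized for. Each arm's success rate would describe those who coped with the taper rather than those randomised. If coping differs by arm, so does the selection. The trial's rationale makes a difference plausible: the Discussion hypothesises that electroacupuncture eases withdrawal symptoms.

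**Working it through.** **1. The plan's own numbers.** The continuity-corrected two-proportion formula with 0.50, 0.1083, two-sided 0.05 and 90% power gives 31.75, so 32, matching the stated 31.7. (The printed arcsine formula, with its constant as a multiplier, gives 25.9; that is a separate matter.) The stated 39 is 32 × 1.2 = 38.4, rounded up. The inflation itself implies that dropouts are expected to supply no primary value.

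**2. What the rule does to a single binary value.** Take an arm with n randomised, m without a value and s successes. With treatment group as the only predictor, a missing value adds nothing to the likelihood, so the estimate is s/(n − m), the complete-case rate.

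**3. Effect on each arm's rate.** If a fraction d drops out and all are failures, a true rate p is read as p/(1 − d). Only d = 20% overall is in the protocol; the splits by arm below are assumptions.

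| Dropout, electroacupuncture/sham | Rates read | Difference | Odds ratio |
|---|---|---|---|
| none (true rates) | 50.0% vs 10.8% | 39.2 points | 8.2 |
| 20/20 | 62.5% vs 13.5% | 49.0 | 10.6 |
| 10/30 | 55.6% vs 15.5% | 40.1 | 6.8 |
| 30/10 | 71.4% vs 12.0% | 59.4 | 18.3 |

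At 20% the factor is 1/0.8 = 1.25.

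**4. Effect on the test.** Simulation with 39 per arm, uncorrected chi-square at two-sided 0.05, no true difference, all dropouts failures:

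| True success, both arms | Dropout by arm | Complete-case type I error | Dropouts counted as failures |
|---|---|---|---|
| 30% | 20/20 | 5% | 5% |
| 30% | 25/15 | 7% | 5% |
| 30% | 30/10 | 12% | 5% |
| 10.83% | 30/10 | 7% | 6% |

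With true rates of 35% vs 15% (also assumed), complete-case power is 82% if electroacupuncture loses 30% and sham 10%, and 32% if the split is reversed. Counting failures gives 55% either way. At the protocol's 50% vs 10.83%, complete-case power is about 93% or more under either 30/10 split.

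**5. The reverse case.** If dropout is unrelated to outcome (30% success in both arms, dropout 30/10), complete cases keep 5% type I error, and counting every dropout as a failure gives 9.7%.

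**6. Power when dropouts count as failures.** If the planning rates refer to completers and 20% drop out as failures, the rates become 0.8 × 50 = 40% and 0.8 × 10.83 = 8.7%. At 39 per arm, exact power is 88.5% (Fisher) and 92.8% (chi-square).

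**The case against.** **The article does not say that taper failures leave the denominator.** A reader might infer that it does. It names intention-to-treat, its full analysis set keeps anyone with one session and one post-baseline assessment, and counting a failed taper as not discontinued would fit the outcome definition. The rule's wording is tied to mixed models, so one can argue that the primary outcome is left to an analysis plan not shown. This stands in part: removal is a consequence of the stated rule, not a sentence in the text. But the rule covers missing outcome data in general, exempts nothing, and is the only one given.

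**Multiple imputation could do better than complete cases.** The medication diary is kept weekly, and dose reduction, withdrawal symptoms and craving are recorded at weeks 2 and 4. An imputation using them would help, and the imputation model is not described. As ordinarily run, it still assumes missing at random.

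**Not every withdrawal is a failure.** This stands. Starting an anxiolytic is not NBZD use. Missing more than half of 18 sessions means missing at least 10, which at three a week can be certain only from week 4, when a taper of 25% of baseline per week may already have reached zero. Only criterion 1 clearly marks a failed taper.

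**The test is not generally invalid.** This also stands. Equal dropout keeps the type I error, and the 12% needs a threefold imbalance with every dropout a failure.

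**The two sections on intolerable symptoms may be graded.** A reader might see a flat contradiction. The withdrawal criterion adds the word severe, so reverting first and withdrawing later is a possible reading. No boundary is stated, however.

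**Conclusion.** The concern holds in limited form. The stated rule does not fit the primary outcome, at least one withdrawal route is tied to that outcome by its own wording, and no analysis departs from missing at random.

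Each arm's success rate is overstated to the extent that failed tapers drop out: by 1.25 at 20% dropout if all are failures. Bias in the test requires withdrawals that differ by arm. Its size is unknown because the protocol gives only an overall dropout rate, and its direction is not fixed. If electroacupuncture eases withdrawal as hypothesised, more sham failures would be lost. In the 10/30 example that lowers the odds ratio from 8.2 to 6.8 and barely moves the risk difference.

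The documents do not support saying that the type I error is lost as a rule, that all withdrawn participants are non-discontinuers, or that the protocol prescribes their removal. Separately, the boundary between symptoms that lead to dose reversion and symptoms that lead to withdrawal is undefined. The same event could therefore become a counted failure or a missing value.

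**What to change.** Under Data management and Statistical analysis, add a rule for the primary outcome:

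1. Analyse the randomised participants, with those withdrawn under criterion 1, or known to be still using NBZDs, counted as not discontinued.
2. As the primary rule, count others without verified data for days 36–42 as not discontinued too.
3. Replace missing-at-random multiple imputation as the sole check with a tipping-point analysis that varies these participants' success probability separately by arm.
4. Keep collecting the existing medication diary after withdrawal, where consent allows.
5. Reconcile Withdrawal criteria with NBZDs tapering protocol on intolerable symptoms and state the boundary. Which action applies is for the investigators to decide.

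**Cost:** mainly wording, plus continued diary collection; no larger sample under the protocol's own assumptions. Reported success rates fall somewhat (for example 40% vs 8.7%), with power still about 88–93%. The rule in item 2 has its own risk: if dropout is unrelated to outcome and unequal by arm, it is biased (9.7% type I error at 30/10). The tipping-point analysis is there to show whether the conclusion depends on it.
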